### 2.3. Sample Size

For the present study, a minimum size of 21 subjects per group is required to obtain a difference of at least 5 BoHA units at a significance level of 0.05 and a power of 80%. Considering a possible dropout of 20%, at least 27 subjects per group will be recruited, for a total sampling of at least 54 children with diplegic Cerebral Palsy. The minimum sample size was computed using the G*Power software v 3.1 9.6.

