In this direction, a systematic review [12] collected fifteen studies, which presented a wide variety in the intervention content and in the outcome measures, impeding a meaningful synthesis of results. Among the analysed studies, a good quality is reached by the HABIT or HABIT-ILE treatment [13,14], which showed to have a role in promoting the UL skills, but with particular respect to the dominant hand. These authors reported that this could be due to the role of the two hands in gross motor activities and the need of the ULs, and particularly the non-dominant one, to support the stabilization of the posture. In addition, the selected primary outcome measure Both Hands Assessment (BoHA) may not be sufficiently sensitive to detect changes in the magnitude resulting from the HABIT intervention in relation to participants’ characteristics. There is also an example of a technological intervention specifically focused on UL skills in children with diplegic CP that is proposed (Armeo^®^ Spring): in a pilot study [15], it resulted in an improvement at clinical scales, often transferred also in everyday life activities in areas not directly trained, such as self-care, suggesting that the technological context highly enhances the motivation.

Anyway, the aforementioned review [12] suggests that further studies are needed, by respecting a high-quality methodology, by isolating the intervention under exam and avoiding interventions that comprise more than one component, and by selecting the specific population on the basis of specific classification systems. Finally, they sensibilize on the use of appropriate outcome measures.

In addition to this, to our knowledge, an aspect that seems to be lacking is the inclusion and investigation of extra motor factors, since the motor impairments are shown to be mostly caused and/or accompanied by extra motor factors [16], such as the visual-perceptual impairment [17] and the altered sense of agency [18]. More specifically, diplegic CP causes impairments in the acquisition, integration, and interpretation of multisensory information originating from both somatic and environmental sources. Such impairments are particularly evident in processing spatial and temporal characteristics of sensory input, which constitute critical substrates for the planning, modulation, and execution of purposeful and coordinated motor behaviour [19,20,21,22].

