## 2. Materials and Methods

### 2.1. Study Design

The project is a non-profit two-arm exploratory randomized clinical study consisting of an experimental group and a control group. Recruitment, clinical experimentation, and analysis of all clinical, technological, and neuroimaging data will be carried out by the centres involved in the study: IRCCS Fondazione Stella Maris (Pisa), AUSL IRCCS of Reggio Emilia, University of Parma. The recruitment will be carried out by some staff members (who will not have access to the allocation sequence), which will be responsible for the identification of eligible children; then, a different group of staff members will take care of randomly assigning the enrolled children to the study groups.

After fulfilling the inclusion and exclusion criteria described below and obtaining signed informed consent, enrolled participants will undergo an initial baseline assessment (T0) and will be block-randomized (ratio 1:1) in the experimental group (EG) or the control group (CG), using a computer-generated set of random numbers by an independent operator. The EG will carry out an 8-week AOT period, while the CG will continue standard care; that is, they will continue their usual care without receiving any additional training (details in Section 2.5).

Families from both groups will be asked to complete a diary to track daily activities and therapies throughout all 8 weeks. After this period, both groups will be assessed again (T1). T1 will be the primary endpoint aimed at evaluating the short-term effects of AOT. All participants will also be evaluated at 8 and 24 weeks (T2 and T3, respectively) after T1 (Figure 1) to evaluate the medium- and long-term effects of AOT. Details of the AOT training and the adopted outcome measures are described below.

The clinical team asked the FTS foundation—an association composed of families of children with CP—for support in participant enrolment and involvement. They are actively participating in this study, particularly in awareness campaigns and participant enrolment. After the study’s completion, the FTS foundation will help the consortium involve families in reporting their experiences and be informed about the study results in a joined final event.

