### 2.2. Participants

Participant recruitment will be conducted by the two clinical centres involved in the project, in accordance with predefined inclusion and exclusion criteria (IRCCS Fondazione Stella Maris and AUSL IRCCS of Reggio Emilia), selected within databases that collect data of subjects who have previously given consent to receive information and proposals for new research protocols, and among patients referring to the above-mentioned structures for functional assessments and/or rehabilitation care. Eligible subjects and their families will subsequently receive invitations to participate in the study, and informed consent will be obtained from the subjects and/or their caregivers before enrolment. Subjects will be recruited based on the following specific inclusion criteria:Confirmed diagnosis of spastic diplegic Cerebral Palsy;Age between 5 and 16 years at the time of recruitment;Manual Ability Classification System (MACS) levels I–III [39];Gross Motor Functional Classification System (GMFCS) levels I–III [40];At least one cognitive functioning index greater than −2 standard deviations, assessed with a battery of standardized tests such as WISC-IV or WISC-V, in order to ensure a sufficient level of comprehension and cooperation in the proposed activities.

Moreover, the following exclusion criteria will be applied:Presence of uncontrolled epilepsy;Injection of botulinum toxin or orthopaedic surgery in the upper limb carried out in the previous 6 months or planned during the study period.

Participants will be removed from the study regardless of their allocation group if any of the following conditions are met:They begin an intensive treatment program;They require a botulinum toxin injection before the end of the study;Other adverse events occur that prevent further participation.

A subgroup of patients from EG and CG will be selected to perform a functional magnetic resonance imaging (fMRI) assessment. For these participants, additional exclusion criteria will be the following:Insufficient cooperation during approximately 30 min long neuroimaging studies;Presence of exclusions for 3T MRI investigations (as metal implants, prostheses, shunts, etc.). These exclusions will be checked using an ad hoc questionnaire.

Moreover, a subgroup of age-matched typically developing (TD) children, recruited on a voluntary basis, will be also enrolled as healthy control group.

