### 2.8. Statistical Analyses

A descriptive statistical analysis (mean, standard deviation, and frequencies) will be conducted for both EG and CG. Initially, differences between the two groups at T0 will be examined for the various outcome variables, assessing the significance of the results through *p*-values. Depending on the data distribution, parametric or non-parametric tests will be applied. Subsequently, intergroup differences at the primary endpoint (T1) will be analysed. A second level of analysis will be performed to assess differences between follow-up and baseline evaluations. Additionally, Cohen’s d effect sizes and their 95% confidence intervals will be calculated to quantify the magnitude of the effects.

All clinical, neurophysiological, and technological data collected at baseline will be correlated with the outcomes to identify predictive markers of training response. Specifically, a two-stage procedure will be followed: (i) a LASSO-based variable selection method will identify the parameters most strongly associated with changes, and (ii) a statistical model will be developed based on the selected variables. The model will be quantified and optimized using cross-validation and bootstrap techniques.

The preprocessing of functional images will be performed using the SPM12 software, implementing routines for spatial realignment, slice-timing correction, anatomical-functional coregistration, segmentation, and normalization to the MNI template. Group-level statistical analyses will be conducted using the General Linear Model, which will be employed to calculate the main effects of experimental and control conditions (t-contrast). Subsequently, to assess the contribution of each experimental condition and activation differences for each subject, a Region of Interest (ROI) analysis will be performed in key areas of interest, extracting the BOLD signal associated with each condition. To evaluate the significance of BOLD signal differences within conditions (within-subject effects) and between groups (between-group effects), a Repeated Measures Analysis of Variance (rmANOVA) will be applied. All statistical parametric maps will be corrected for multiple comparisons using the Family-Wise Error (FWE) method.

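### The 80% power claim implies an unstated BoHA SD of about 5.6, and the T1 comparison it must serve names no baseline adjustment; adjust for T0 BoHA and restate the power

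*Protocol article*

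**What the plan says.** Section 2.3 states that "a minimum size of 21 subjects per group is required to obtain a difference of at least 5 BoHA units", with alpha 0.05 and 80% power, and adds that "The minimum sample size was computed using the G*Power software v 3.1 9.6". It allows for losses: "Considering a possible dropout of 20%, at least 27 subjects per group will be recruited", which makes 54 in total. It gives no SD, standardised effect size, test or sidedness. It does not say whether the 5 units refer to T1 scores, to change from T0, or to baseline-adjusted scores.

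Section 2.6 names BoHA as the primary outcome and, by its general rule, has it measured at every timepoint. Section 2.1 makes T1 the primary endpoint. On the analysis, Section 2.8 first compares the groups at T0 and then says: "Subsequently, intergroup differences at the primary endpoint (T1) will be analysed". The choice between parametric and non-parametric tests depends on the data distribution. Differences between follow-up and baseline come under a second level of analysis. No covariate is named for the T1 comparison.

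On eligibility, Section 2.2 admits "Manual Ability Classification System (MACS) levels I–III" and ages 5 to 16 years.

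**The concern.** A power statement in raw units depends on the SD of the quantity analysed. Once n, the difference, alpha and power are fixed, that SD is fixed too, apart from the choice of a one- or two-sided test. The implied value can therefore be recovered and set beside the analysis described.

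Read plainly, Section 2.8 compares T1 scores between the arms and leaves change from baseline to a second step. The SD that governs power is then the spread between children at T1, in a sample that covers three grades of manual ability and a wide age range. A change score or baseline-adjusted residual can have a much smaller SD than the raw score when T0 and T1 are strongly correlated. The same 5-unit target can thus be well powered under one analysis and poorly powered under another, and the article does not say which one its figure belongs to.

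At stake is how the trial will be read. If the T1 comparison has much less than 80% power for 5 units, a non-significant result could be taken as evidence against the training when the comparison could not settle the question.

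**Working it through.** **Inputs from the article.** Difference 5 BoHA units, alpha 0.05, power 80%, n = 21 per group, dropout 20% (Section 2.3); allocation 1:1 (Section 2.1). The SD is not given. Every SD and correlation used in steps 3 to 5 is an assumption.

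**1. Dropout step.** 21 / (1 − 0.20) = 26.25, rounded up to 27 per group, 54 in total. This reproduces the stated figures.

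**2. Implied SD.** The figure of 21 cannot be reproduced forwards without an SD, so it is solved backwards. For a two-sample t-test (noncentral t) with n = 21 per group and 80% power:
- two-sided: d = 0.886, so SD = 5 / 0.886 = 5.64 (SDs from about 5.50 to 5.64 all round up to 21 per group);
- one-sided: d = 0.781, so SD = 5 / 0.781 = 6.40;
- two-sided rank test, with asymptotic relative efficiency 0.955 under normality: SD about 5.51.

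**3. Power if the analysed SD is larger** (two-sided t-test, difference 5 units):

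| Assumed SD | 21 per group | 27 per group |
|---|---|---|
| 5.64 | 80% | 89% |
| 6 | 75% | 85% |
| 8 | 51% | 62% |
| 10 | 35% | 44% |
| 12 | 26% | 32% |

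The last column is the case with no losses.

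**4. Detectable difference** at 80% power with 21 per group = 0.886 × SD: 7.1 units at SD 8, 8.9 at SD 10, 10.6 at SD 12.

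**5. Effect of adjusting for T0.** In an ANCOVA the residual SD is about SD × sqrt(1 − rho²), where rho is the T0–T1 correlation. Roughly 80% is kept when this is at most about 5.64, that is, when rho is at least sqrt(1 − (5.64 / SD)²):
- SD 8: sqrt(1 − 0.497) = 0.71;
- SD 10: sqrt(1 − 0.318) = 0.83;
- SD 12: sqrt(1 − 0.221) = 0.88.

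Below those correlations adjustment still helps. At SD 10 and rho 0.8 the residual SD is 10 × 0.6 = 6.0, and power is about 75% against 35% unadjusted. At SD 10 and rho 0.6 it is 10 × 0.8 = 8.0, and power is about 51%. These figures ignore the one degree of freedom spent on the covariate, which is negligible here.

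**The case against.** The strongest reply is that nothing in the article is shown to be wrong. The one step that can be checked forwards is correct, and no stated figure contradicts 21 per group. The SD, its source and the sidedness are details that a journal article may leave to the full protocol or analysis plan, so their absence alone is no finding. All of that stands.

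Two stronger readings are tempting, and neither is supported. A reader might infer that an SD of 5.6 is unlikely in so mixed a sample. The article gives no BoHA SD, no means by MACS level, no MACS distribution and no T0–T1 correlation. Illustrations built on an assumed mix and an assumed step between levels show only what could happen. A reader might also infer that the sample size was computed for a different analysis from the one described. Section 2.3 does not say which quantity it concerns, and Section 2.8 does not say that raw scores will be compared unadjusted. That is the natural reading, not an explicit statement.

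The Introduction remarks that BoHA "may not be sufficiently sensitive to detect changes in the magnitude resulting from the HABIT intervention". This concerns another programme, is qualified by participants' characteristics, and does not contradict a 5-unit target.

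The trial is also labelled exploratory, and Section 2.8 promises Cohen's d with 95% confidence intervals, which would expose imprecision. If all 27 per group are analysed, the tolerable two-sided SD rises to about 6.44. This softens the consequence without removing it: at SD 8 power is still 62%. A one-sided test would not rescue it either, giving 64% at SD 8 and 48% at SD 10 with 21 per group.

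**Conclusion.** The point holds in a limited form. The 80% power claim implies an SD of about 5.6 units for the analysed quantity (two-sided; about 6.4 one-sided). The primary comparison, as described, does not name the adjustment that would make it most likely to meet that SD. If the comparison is of unadjusted T1 scores and their SD is 8, 10 or 12, power with 21 per group is 51%, 35% or 26%. Those SDs are assumptions, and whether the true value exceeds 5.6 cannot be settled from the document. The conclusion therefore concerns an avoidable exposure in how the primary analysis is fixed. It does not show that the trial is underpowered or that the sample size was miscalculated.

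**What to change.** Keep 27 per group and make three changes.

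1. In Section 2.8, define the primary analysis as an ANCOVA of T1 BoHA on treatment group with T0 BoHA as covariate.
2. In Section 2.3, restate the power for that analysis: two-sided alpha, total SD, T0–T1 correlation and the resulting residual SD, each with its source. Show power over a range (for example total SD 8, 10 and 12 with several correlations) in place of a single 80% figure.
3. State that the T1 difference will be reported in BoHA units with its confidence interval, and that a non-significant result will not be read as absence of effect.

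The cost is revised wording and a short recalculation, with no extra participants or assessments, since T0 BoHA is already collected. The downside is that the restated power may fall below 80%, and the article would then have to say so.

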### 2.4. Experimental Training (AOT)

Before delivering the ACT ON DIP system, the program will be personalized for each child. The rehabilitation staff will select the most appropriate exercises from the library, based on the participant’s characteristics, such as dominant hand, age, manual abilities, and cognitive level. A box containing all the necessary objects will be organized, with each item identified by a number corresponding to the training day (e.g., pencil case number 3, which corresponds to day 3 of training).

Moreover, a dedicated printed manual will be provided, containing instructions and guidelines related to the system installation. The manual will also include all the contact details of the technical and rehabilitation staff for remote assistance for any problems occurring during training.

Together with this material, two Actigraphs (wGT3X-BT) will be delivered for the recording period and worn by the child on each wrist. The whole system will be installed at the participant’s home. Families will be asked to identify a suitable location, with an appropriately sized (approximately 80 × 100 cm) table or desk near an electrical socket, where the computer will be placed. The rehabilitation staff will train the family on the correct use of the system, with particular respect to the safety aspects. During the first 2 days of training, a therapist will assist each family to confirm the correct setup. Subsequent sessions will be remotely supervised by the rehabilitation staff, who will provide feedback and maintain regular contact with the families. During the training sessions, each participant will be seated on a chair with the arms on a table, in front of the computer, in which the ad hoc software will conduct the child through the sequence of observations and the correspondent executions.

The training will be structured in one session a day, 5 days a week, for 8 consecutive weeks. Each session will last approximately 1 h, totalling around 40 h of training, which is intended to be meaningful for inducing change [41]. Participants undergoing the AOT training will have daily sessions with increasing training difficulty. The complexity of each motor sequence and the amount of movement required will increase over time. Each daily session will include four videos shown in first-person point of view: the first three will be three different actions (more specifically, three parts of a larger task, such as (i) placing an object close to the body, (ii) opening a box, and (iii) inserting the object in the box), while the fourth one will consist of the combination of the previous three (i.e., the whole task). For each video sequence, the same video of the single action will be shown seven consecutive times; after which, participants will be asked to perform the observed action themselves seven times in an analogous condition. All the sequences will be watched and performed twice (Table 1).

#### 2.4.1. ACT ON DIP System

The ACT ON DIP system is designed through the collaboration of clinical rehabilitation staff, including physicians, therapists, and psychologists from IRCCS Fondazione Stella Maris, AUSL IRCCS of Reggio Emilia, and the University of Parma, in partnership with engineers and Khymeia (Italy). The main components of the ACT ON DIP system, the exercise library, and the experimental training were built based on previous clinical experiences with UPCAT and TELE-UPCAT.

The ACT ON DIP system, shown in Figure 2, consists of an all-in-one computer, with an ad hoc software, which includes the AOT video library, two age-appropriate narrative contexts that guide the training for children and adolescents (conceptualized and created in collaboration with the FTS foundation), and specific instructions for each training day and activities.

The ACT ON DIP system software operates as follows: a video of the daily task is presented to the participant, after which the participant is asked to execute the action shown in the video. Then, the same video is replayed, and the participant executes the action a second time. At the end of each session, the software automatically loads the next day’s task, uploads the recorded videos to a secure cloud service for clinician review, and shuts down.

A mascot is used to create a narrative context, which guides the patient throughout the training session. It presents the activities, keeps the patient focused on the task, and gives visual rewards.

The system is equipped with two cameras: one to capture the execution phase, providing a comprehensive view of the child, the table, and the object, and another to record the observation phase, focusing on the child’s face and determining whether they are looking at the monitor. To ensure that participants are paying attention to the screen contents, they will be required to wear an IMU sensor inside a headband that will record head movements during the observation phases. Participants will also be asked to wear a pair of wearable sensors (described below) for registering UL movements. Supporting caregivers will also be given a sensor that communicates with the system and allows the activities to progress.

Together with the ACT ON DIP system, the same objects shown in the videos will be provided to the family, as well as the related placemats to facilitate initial object positioning.

#### 2.4.2. AOT Library

Based on previous projects, the clinical staff—composed by a child neuropsychiatrist, developmental therapists, and neuropsychologists—developed a library of rehabilitation packages consisting of different series of AOT exercises suitable for home-based execution. These series differ in complexity, involving the use of different materials and requiring a specific type of movement (i.e., reaching and grasping, handling and manipulating), as well as the use of the dominant hand (right or left), to personalize the training approach. Each series includes sequences designed to perform unimanual and bimanual upper-limb actions, targeting specific goals, using a variety of objects and toys commonly used in daily life. Both series consist of 40 activities, each corresponding to a specific sequence of actions, to be completed in 8 weeks. Each session activity has a general common goal (e.g., preparing the pencil case), composed of three sequential tasks of increasing complexity (e.g., bringing the pencil case closer → opening it and placing the pens inside → closing the pencil case). Each single action and then the overall sum of the three actions are videotaped, performed by a therapist with the upper limbs seen from a first-person perspective. Each video is then edited by repeating the actions 7 times to obtain the final version that will be shown to participants in the EG.

